### Data collection window

Outcome data for all practices will be obtained for the 2-year period from 1 June 2022 to 29 May 2024. This data collection window is lagged behind the trial time window (1 April 2022 to 31 March 2024) in order to: (a) provide some time for practices to become accustomed to how the intervention functions prior to data collection and (b) to have a 2-month window following the end of the intervention window in order to allow cancers to be diagnosed in patients seen towards the end of that window.

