#### Randomisation

Practices will be randomised using a 1:1 ratio into one of two trial arms: usual diagnostic care (control) and usual diagnostic practice plus access to the suite of eRATs, as the intervention. Randomisation will be computer-generated and web-based, conducted by an independent member of staff at the Exeter Clinical Trials Unit (ExeCTU), overseen by the CTU statistician (not the trial statistician). To promote balance between the trial arms in practices’ use of the 2-week wait system, and therefore propensity to refer to secondary care, we will minimise randomisation by age–sex standardised 2-week wait referral ratio (the best available proxy) in national tertiles. We will use simple randomisation to allocate the first 50 practices (~10% of the total target), and then apply minimisation by 2-week wait referral ratio tertile, taking into account the previous allocations to inform the minimisation algorithm. All allocations using the minimisation algorithm will retain a stochastic element, aimed at promoting allocation concealment.

The data analysis will be carried out by the trial statistician and health economist, blinded to treatment allocation, and all primary outcome data are objective assessments of clinical outcome. Staging (the primary outcome) will be performed by pathologists unaware of trial participation or allocation. However, given the nature of the intervention, it is not possible to blind GPs or the GP practice to treatment allocation.

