
### Data collection

All primary and secondary outcome measures are available from NCRAS, Diagnostic Imaging Dataset and publicly available practice level data, including Cancer Waiting Times data. We will be using depersonalised (pseudo-anonymised) data. The Public Health England Office for Data Release guidelines indicated that no legal gateway (eg, section 251 approval) will be necessary to obtain these data.

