### Data analysis

All analyses will follow Consolidated Standards of Reporting Trials (CONSORT) guidelines for cluster-randomised and pragmatic trials. The primary analysis, exploring the proportion of patients with early-stage cancer at diagnosis, will use mixed-effects logistic regression with a random intercept for practice to accommodate the hierarchical nature of the data (ie, random allocation by practice, with participants nested within a practice). This regression will include trial arm at practice level, and will adjust for patient-level covariates known to be associated with stage (age, sex, quintile of the income domain from the Index of Multiple Deprivation (IMD) and cancer site),^37^ and the practice-level minimisation variable (national tertile of age–sex standardised 2-week wait referral ratio). We will further adjust the model at the practice level for list size, clinical IT system used, and Care Quality Commission overall rating, should these variables be associated with stage in preliminary analyses (even if not unbalanced with respect to trial allocation). Trial arm and covariates will all be entered as fixed effects. The degree of change in the percentage of patients diagnosed at a late stage in intervention practices will be investigated by exploring the marginal distributions of trial arm on the probabilities predicted by these models.

For the secondary outcome of the stage at diagnosis of six cancers without eRATs, we will repeat the above model including data on the six non-eRAT cancers as well as the six eRAT cancers. This model will use all the variables described above, plus an indicator variable for whether the cancer site has an eRAT, and an interaction term between this variable and trial arm. From this model, we will obtain odds ratios (with 95% CIs) for (i) the ‘spillover’ effect of having the intervention on cancer sites not included in the intervention, and (ii) for the relative effect of the intervention on stage for included cancer sites compared with those not included in the intervention.

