Mixed-effects logistic regression models with a random intercept for practice will also be fitted for the other secondary binary outcomes; route to diagnosis, conversion rate and timeliness. These models will include trial arm as a practice-level effect, and will adjust at the patient level for age, sex and quintile of the IMD income domain, and at the practice-level for the minimisation variable (national tertile of age–sex standardised 2-week wait referral ratio). These analyses will also adjust at the patient level for cancer site (routes to diagnosis analyses) or for referral type (2-week wait analyses) as appropriate. The models will be further adjusted as in the main outcome variable analysis.

Time-to-event secondary outcomes (length of waiting time, survival) will be analysed using mixed-effects parametric survival models with a random intercept for practice, and all other variables added as fixed effects. These models will include trial arm as a practice-level effect, and will adjust for the same patient-level factors as described above (waiting times adjusted for referral pathway rather than cancer site as above), and the practice-level minimisation variable (national tertile of age–sex standardised 2-week wait referral ratio). The models will also use the same adjustment as the primary outcome measure. An appropriate distribution to model the baseline hazard will be used, as determined by a comparison of the Akaike information criteria under different distributions.^38^

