For rate outcomes (number of 2-week wait referrals, cancers and imaging investigations), we will analyse the rates per 100 000 registered patients per year by age–sex strata using mixed-effects Poisson regression models including a random intercept for practice. These models will include trial arm as a predictor and will adjust for the age and sex of the strata, and at the practice level for the minimisation variable (2-week wait referral ratio) and deprivation (quintile of IMD overall score). The models will be further adjusted at the practice level for list size, clinical IT system used, Care Quality Commission overall rating, and for the age and sex case mix of practices should these covariates be found to be associated with the outcome (even if not unbalanced with respect to allocation). Case mix will be incorporated by including variables for counts of practice populations in different age–sex strata (5-year age groups by sex, excluding one age–sex stratum that can be determined once all others are known).

All the above analyses will combine data for the six eRAT cancers for each model. For outcomes related to 2-week wait referrals, data will be combined for all referral pathways relevant to the six eRAT cancers. To investigate whether the eRATs produce a spillover effect, whereby diagnostic activity is increased for other cancers, we will repeat all analyses using data for the six non-eRAT cancers combined for each model. Investigation of a spillover effect for 2-week wait referral outcomes will use data for all referral pathways combined.

Additional sensitivity analyses will be conducted for the primary outcome in order to explore moderation arising from practice-level characteristics, using interaction terms. Although the trial has not been powered to detect low-to-moderate subgroup differences, such as differences in a single cancer site, large interaction effects that differ with respect to the direction of effect across subgroups are of interest. The potential impact of missing staging data on the primary outcome will also be explored through use of multiple imputation methods making use of auxiliary variables, such as survival time, morphology and grade, to improve the missing at random assumption in line with previous work).^37^

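### The primary model uses no pre-trial practice-level stage value, a cheap gain in precision if the registry can supply one and practice patterns persisted

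*Protocol article*

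**What the plan says.** All references are to the protocol article.

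- **Data analysis, primary model.** A logistic model with a random intercept for practice "will adjust for patient-level covariates known to be associated with stage": age, sex, income-deprivation quintile and cancer site. At practice level it includes "the practice-level minimisation variable (national tertile of age–sex standardised 2-week wait referral ratio"). It goes on: "We will further adjust the model at the practice level for list size, clinical IT system used, and Care Quality Commission overall rating", if these prove associated with stage. No pre-trial value of the stage outcome appears.
- **Data analysis, other patient-level models.** The binary and time-to-event secondary outcomes use the same "national tertile of age–sex standardised 2-week wait referral ratio".
- **Data analysis, rate models.** Adjustment is "at the practice level for the minimisation variable (2-week wait referral ratio) and deprivation (quintile of IMD overall score"). The word tertile is not repeated here.
- **Randomisation.** The ratio was used for allocation in grouped form: "we will minimise randomisation by age–sex standardised 2-week wait referral ratio (the best available proxy) in national tertiles".
- **Data collection window.** "Outcome data for all practices will be obtained for the 2-year period from 1 June 2022 to 29 May 2024". No earlier extract is mentioned.
- **Data collection.** "All primary and secondary outcome measures are available from NCRAS, Diagnostic Imaging Dataset and publicly available practice level data". The Primary outcome section says that stage is routinely collected by the national registry, and it gives a 2018 national early-stage percentage.

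**The concern.** In a cluster trial, only practice-level information that predicts a practice's result can reduce the between-practice part of the variance through adjustment. The practice's own earlier result is a natural candidate. The plan relies instead on a three-level referral proxy and three optional structural variables.

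What is at stake is the width of the confidence interval for the primary odds ratio. The Sample size section itself calls the target difference quite large and says that a much smaller one would still be clinically valuable, so precision that costs little is worth having. It would also give some protection if more practices are lost than the 10% allowed for.

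A second, smaller matter concerns the number of 2-week-wait referrals. For that outcome the standardised referral ratio is in effect a baseline of the outcome, so the form in which it enters the rate models matters more than it does elsewhere.

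**Working it through.** **Inputs from the Sample size section.** ICC 0.05; mean cluster size m = 23; coefficient of variation of cluster size 0.7; 90% power at α = 0.05 (two-sided assumed); 2049 patients per arm before clustering; 478 practices before loss.

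**Assumed, because the protocol does not give it.** Cluster autocorrelation (CAC), the correlation of a practice's true effect between the baseline and trial periods. The range shown is 0 to 0.9.

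**1. The plan's own figures.** Design effect = 1 + [(0.7² + 1) × 23 − 1] × 0.05 = 2.66, as stated. 2049 × 2.6635 = 5458, against the stated 5497 (0.7% apart). 5497 / 23 = 239 per arm, so 478 in total. The planned power is therefore taken as 90% at 478 practices.

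**2. Share of a practice mean's variance that is between practices.** 23 × 0.05 / (1 + 22 × 0.05) = 1.15 / 2.10 = 0.548.

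**3. Effect of a baseline covariate, equal cluster sizes.** On a scale where total individual variance is 1:

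- Without baseline: 0.05 + 0.95/23 = 0.0913.
- With baseline: 0.05 × (1 − CAC² × R) + 0.95/23, where R is the reliability of the baseline mean. Two baseline years with about 23 cases give R = 0.548.
- Example, CAC 0.7: 0.05 × (1 − 0.49 × 0.548) + 0.0413 = 0.0779; ratio 0.0779 / 0.0913 = 0.853.
- Power = Φ[(1.960 + 1.282)/√ratio − 1.960]. At 0.853 this is Φ(1.55) = 93.9%.

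**4. Unequal cluster sizes.** Gamma sizes with mean 23 and coefficient of variation 0.7, mixed-model weights, two baseline years, ICC 0.05:

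| CAC | Variance factor | Power at 478 practices |
|---|---|---|
| 0 | 1.00 | 90% |
| 0.5 | 0.92 | 92.3% |
| 0.7 | 0.84 | 94.4% |
| 0.8 | 0.78 | 95.6% |
| 0.9 | 0.72 | 96.9% |

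With one baseline year and CAC 0.5 to 0.8, the factor is 0.94 to 0.84 and power is 91.7 to 94.2%.

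**5. Lower ICC.** At ICC 0.02, R = 0.46 / 1.44 = 0.319. With equal sizes the reduction is CAC² × R²: 4% at CAC 0.6, 7% at 0.8 and 10% at 1.0.

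**6. Detectable odds ratio.** Scaling log 0.8 by the square root of the variance factor gives exp(ln 0.8 × √0.92) = 0.81 and exp(ln 0.8 × √0.78) = 0.82.

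**7. Tertiles against a continuous ratio.** For a normal covariate, tertiles keep 6φ(z)² of the linear explained variance, with z the upper tertile point: 6 × 0.3636² = 0.793.

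- *Stage.* Suppose the ratio explains 2 to 20% of between-practice variance (assumption). The variance factor, continuous over tertile, is 0.998 to 0.975, so power rises by 0.1 to 0.7 points.
- *Referral rate.* Suppose baseline and follow-up correlate at 0.6 to 0.8 (assumption) and the rate models use tertiles alone. Residual between-practice variance changes by (1 − r²)/(1 − 0.793r²) = 0.896 to 0.731, a cut of 10 to 27%.

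**The case against.** The case against has real weight.

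- **Nothing is wrong with the planned model.** It adjusts for the minimisation factor in the form used for allocation, which is accepted practice, and the trial is sized for 90% power without any baseline covariate. This stands. A reader might infer that the analysis is biased or the trial underpowered; the document supports neither.
- **The size rests on an unknown autocorrelation.** Pre-pandemic baseline years would end more than two years before June 2022, with the pandemic in between, so a low value is plausible. The patient-level covariates may also already absorb some between-practice variance. This stands, and it is why the gain is given as a range that reaches zero.
- **The detectable odds ratio barely moves**, from 0.80 to about 0.81 to 0.82. Correct, though the added power costs little.
- **Availability is inferred.** The Data collection section says that outcome measures are available; it does not mention a pre-trial extract by practice. The fix is therefore conditional.
- **An ICC of 0.05 means that 5% of individual variance is between practices.** True. The 55% applies to practice means, which is the level at which arms are compared.

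Two stronger readings of the tertiles are also tempting. One is that grouping the ratio costs appreciable precision for the primary outcome; under the assumptions shown it costs less than one power point. The other is that the 10 to 27% figure applies to every 2-week-wait outcome. It fits only the referral rate, and the paragraph on rate models does not say that the ratio is grouped there. Conversion, days to diagnosis and the 28-day standard are not follow-up values of a referral ratio.

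**Conclusion.** The point holds as a low-cost improvement, not as an error. The primary model names its covariates and has no pre-trial practice-level stage value. Adding one, based on about two years, would lower the variance of the arm effect by about 8 to 22% and raise power at 478 practices from 90% to about 92 to 96%. This assumes the planned ICC of 0.05, 23 cases per practice and a cluster autocorrelation of 0.5 to 0.8. The last of these is not in the document. The gain shrinks with a lower ICC or a disrupted baseline and vanishes if practice effects did not persist. That the registry could supply the value is a reasonable inference from its routine role, not a documented fact.

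The form of the referral ratio is a side issue: potentially useful in the referral-rate models, nearly immaterial for stage.

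**What to change.** 1. **Primary model.** Before unblinding, prespecify the practice's pre-trial early-stage proportion for the six cancers as a practice-level covariate, if the registry can supply it. Use about two years, smoothed or shrunken because counts per practice are small. State the window. It should end before allocation: recruitment began in August 2019 and software installation was planned to finish by the end of March 2022, so a window close to 1 April 2022 could fall after randomisation in some practices. Keep the planned model without this covariate as a sensitivity analysis.
2. **Referral-rate models.** State the form of the ratio, and enter the log of the standardised 2-week-wait ratio as a continuous covariate alongside the tertile factor. The same change in the stage model is optional.

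**Cost.** The first item needs one extra practice-level aggregate in the registry request. The second should need no new data, since a numeric ratio must have existed to form the tertiles. Neither affects the validity of the planned analysis.

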### Sample size

There are around 130 000 new diagnoses of the six included cancers in the UK annually.^31^ As each of our six cancer sites has different proportions diagnosed at an early stage, the sample size calculation is based on a relative improvement in staging, using an OR of 0.8 for a cancer being diagnosed at stage 3/4 in the intervention arm compared with the control arm. This difference is quite large and equates to an absolute reduction of 4.8% in the intervention arm as an incidence-weighted figure across the six cancers. A much smaller improvement would still be clinically valuable but would necessitate an impossibly large trial.

For the inflation factor we have used an intracluster correlation coefficient based on our previous work, of 0.05.^32^ An average cluster size of 23 patients with a diagnosed cancer with recorded stage during 2-year follow-up is expected, with a coefficient of variation for cluster size of 0.7, giving a design effect of 2.66. For an individually randomised trial with 90% power and an α threshold of 0.05, the sample size would be 2049 patients per arm. Adding in the design effect, this becomes 5497 patients, requiring 239 practices per arm, and 478 practices in total. Owing to changes in practice structure (such as practice mergers, closures or divisions), we anticipate the loss of up to 10% of recruited practices over the course of the trial; to account for this we will recruit a target of 530 practices overall, expecting 12 190 patients to be diagnosed with cancer in total.

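### The eRAT-versus-non-eRAT relative effect on stage is estimated with only a practice random intercept, so its confidence interval is too narrow unless practice effects are identical for the two cancer groups

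*Protocol article*

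**What the plan says.** All of this is in the protocol article, under Data analysis.

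- The primary analysis "will use mixed-effects logistic regression with a random intercept for practice to accommodate the hierarchical nature of the data". On the remaining terms, it says "Trial arm and covariates will all be entered as fixed effects".
- For the comparator cancers, "we will repeat the above model including data on the six non-eRAT cancers as well as the six eRAT cancers", "plus an indicator variable for whether the cancer site has an eRAT, and an interaction term between this variable and trial arm".
- Two odds ratios with 95% confidence intervals are to come from this joint model: (i) the spillover effect on cancers outside the intervention, and (ii) an odds ratio "for the relative effect of the intervention on stage for included cancer sites compared with those not included in the intervention".
- Later in the same section a separate analysis is added: "we will repeat all analyses using data for the six non-eRAT cancers combined for each model".

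The random part of the joint model is thus stated, by reference to the primary model. No random slope, practice-by-group effect or robust standard error is mentioned.

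**The concern.** Arm is constant within a practice, and the eRAT indicator differs between patients of the same practice. The interaction compares arms on a within-practice contrast: the log odds of advanced stage in eRAT cancers minus that in non-eRAT cancers. A shared practice intercept essentially cancels from this contrast. The uncertainty that remains should include how much the contrast itself varies between practices, because practices are the units randomised. A model with one intercept sets that variation to zero.

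The error can run in only one direction. If practices differ in the contrast, the reported standard error for (ii) is too small. What is at stake is the reading of (ii), which shows whether any change in stage is specific to the cancers the tools cover. Spillover has a second estimate from the separate non-eRAT analysis; the relative effect has none.

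**Working it through.** **1. The plan's own figures (Sample size).** With mean cluster size 23, CV 0.7 and ICC 0.05:

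Design effect = 1 + ((0.7² + 1) × 23 − 1) × 0.05 = 2.6635 (stated: 2.66).

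2049 × 2.6635 = 5458 patients per arm, and 5458 / 23 = 237.3 practices. The protocol states 5497 (= 239 × 23) and 239, so the difference is 0.7%. The inputs are therefore read correctly. The protocol gives no figure for the interaction.

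**2. Further inputs.**
- Practice variance on the logit scale: 0.05/0.95 × π²/3 = 0.173.
- Advanced stage in eRAT cancers: 65%, since 35% are early (Primary outcome).
- Advanced stage in non-eRAT cancers: 25%. This is an assumption. Overall 55% are early, and eRAT cancers are about half of all cancers, so 0.5 × 35% + 0.5 × x = 55% gives x = 75% early.
- Non-eRAT cancers per practice: 23, or 1.3 times the eRAT number (assumptions).
- ρ, the correlation between a practice's effects on the two groups: not given, so varied from 1 to 0.

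**3. Hand check of the omitted variance.** The practice contrast has variance 2 × 0.173 × (1 − ρ). Over two arms of 239 practices, with (1 + CV²) = 1.49 for unequal sizes, the part left out of the interaction's variance is about

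2 × [2 × 0.173 × (1 − ρ)] × 1.49 / 239 = 0.00431 × (1 − ρ).

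The reported variance at ρ = 1 is 0.0613² = 0.00376. At ρ = 0.5 the true standard deviation should then be about √(0.00376 + 0.00216) = 0.077. The simulation below gives 0.076.

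**4. Simulation under no effect.** There were 2000 trials per row, with 478 practices and equal numbers of eRAT and non-eRAT cancers. The model had a practice random intercept, arm, indicator and their interaction (without the plan's other covariates), fitted by maximum likelihood with a Wald test at 1.96.

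| ρ | Reported SE, (ii) | True SD, (ii) | Type I error, (ii) | Same, practice-level robust SE | Type I error, (i) spillover |
|---|---|---|---|---|---|
| 1 | 0.061 | 0.062 | 5.4% | 5.2% | 5.0% |
| 0.9 | 0.061 | 0.065 | 6.7% | 5.7% | 4.9% |
| 0.8 | 0.061 | 0.068 | 7.9% | 5.2% | 5.4% |
| 0.5 | 0.061 | 0.076 | 11.4% | 5.8% | 7.1% |
| 0 | 0.060 | 0.087 | 17.8% | 5.0% | 9.5% |

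Simulation error is about 0.5 points near 5% and 0.9 points near 18%. With 1.3 non-eRAT cancers per eRAT cancer, the error for (ii) is 4.4%, 7.9%, 12.4% and 18.1% at ρ = 1, 0.8, 0.5 and 0. Smaller sets of simulated trials gave 12.5% (1500 trials) and about 13% (300 trials) at ρ = 0.5.

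**5. Sensitivity to the ICC.** There were 1500 trials per cell, and the two lower ICC values are assumptions.

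| Residual ICC | (ii) at ρ = 0.8 | (ii) at ρ = 0.5 |
|---|---|---|
| 0.05 | 8.3% | 12.5% |
| 0.02 | 6.8% | 7.5% |
| 0.01 | 6.4% | 6.6% |

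**The case against.** The strongest reply is that the size rests on two unknowns. No section gives ρ. The ICC of 0.05 is a planning value for the six eRAT cancers, whereas the fitted model adjusts for site, age, sex, deprivation and referral tertile, so the residual practice variance may be smaller. Both points stand. The document gives reasons to doubt ρ = 1, but no data: the eRAT sites were chosen partly for frequent emergency presentation, while the comparators include breast cancer, for which the Introduction describes effective screening.

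It can also be said that (ii) is a secondary quantity with no stated test or decision rule, that it is not itself listed among the secondary outcomes, and that an SAP may refine the model. The first two points limit the importance. The third does not remove the point, because the article states the random structure rather than leaving it open.

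A reader might infer more than the document supports:

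- **That excess false positives are certain.** They require ρ below 1.
- **That the spillover interval is equally at fault.** Its error stays at about 5–7% for ρ of 0.5 or more. The separate non-eRAT analysis also does not force one practice effect on both groups.
- **That the model cannot be estimated because the indicator is a sum of the cancer-site terms.** The indicator's main effect is redundant and one column drops out, but neither promised odds ratio changes.
- **That the planned moderation analyses share the fault.** They concern practice-level characteristics, which lie wholly between practices. A single cancer site is mentioned only as an example of a difference the trial is not powered to detect.

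**Conclusion.** The point holds conditionally, and for odds ratio (ii). Unless a practice's effect on stage is the same for both cancer groups, the planned model understates the standard error of the relative effect. At ICC 0.05 the reported standard error should be multiplied by about 1.11 at ρ = 0.8 (0.0676/0.0611) and 1.25 at ρ = 0.5 (0.0758/0.0608). The false-positive rate is then 8% and 11–13% respectively. With a residual ICC of 0.01–0.02 it is about 6.5–7.5%. These figures assume about as many non-eRAT as eRAT cancers per practice and equal practice variance in the two groups.

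This is a modest to material fault in a secondary analysis. The primary analysis and the sample size are not affected.

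**What to change.** In the 12-cancer model, add a practice-level random slope for the eRAT indicator, correlated with the intercept. Separate, correlated practice effects for eRAT and non-eRAT cancers are an equivalent way to write it. Alternatively, keep the model and use practice-level robust standard errors. In the simulations these brought the error for (ii) to between 4.3% and 5.8% in every scenario. The random-slope version was not simulated.

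The change needs one sentence in the analysis plan and no new data. The random-effects version adds one or two variance parameters. The interval for (ii) becomes somewhat wider where practices do differ: at ρ = 0.5 and ICC 0.05 the standard error rises from 0.061 to 0.076. If ρ is 1, little is lost; the robust standard error there equals the model-based one to three decimals (0.061).

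### Case mix in the rate models is coded as stratum counts, which mix practice size with age-sex composition; proportions would fit the model and the stated reason for dropping a stratum

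*Protocol article*

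**What the plan says.** The paragraph on rate outcomes in the protocol article (Methods and analysis, Data analysis) covers 2-week wait referrals, cancers and imaging investigations. Four of its statements bear on this point.

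- **Outcome and model.** "we will analyse the rates per 100 000 registered patients per year", by age-sex stratum, using "mixed-effects Poisson regression models including a random intercept for practice".
- **Fixed adjustment.** The model always "will adjust for the age and sex of the strata", and also adjusts for the minimisation variable and practice deprivation.
- **Conditional adjustment.** "The models will be further adjusted at the practice level for list size, clinical IT system used, Care Quality Commission overall rating" and age-sex case mix, each of these only if it proves to be associated with the outcome. The form in which list size would enter (linear or categorised) is not given.
- **Coding of case mix.** "Case mix will be incorporated by including variables for counts of practice populations in different" age-sex strata (5-year bands by sex), omitting one "stratum that can be determined once all others are known".

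**The concern.** Case mix means composition: what share of the list falls in each age-sex group. A count is composition multiplied by list size. In a model for a rate, size has already been divided out of the outcome, so a covariate that scales with size is poorly matched to what it is meant to represent.

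Three things follow.

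1. Practices with the same mix but different list sizes receive different case-mix values.
2. List size and case mix are listed as separate candidates, each admitted on its association with the outcome. With counts, an association with size alone can admit case mix, so the rule does not separate the two.
3. The justification for omitting a stratum matches proportions, which sum to 1. Counts sum to list size, and list size may not be in the model.

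At stake is some precision in the secondary rate outcomes. These include the investigation rates which, under Secondary outcomes, stand in for adverse events that routine data cannot supply.

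**Working it through.** The protocol gives no power, variance or precision figure for the rate models, so there is no stated figure to reproduce. Three checks apply.

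**1. What the coding implies (exact).** Let practice j have list size L and share p_k in stratum k, so the count is N_k = L·p_k. The case-mix part of the log rate is

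Σ b_k·N_k = L·Σ b_k·p_k.

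For lists of 5,000 and 20,000 with identical shares, every N_k differs by 20,000/5,000 = 4, and so does the whole case-mix term. Adding a linear list-size term gives L·(c + Σ b_k·p_k). The effect of a given difference in mix is still forced to be four times as large, on the log scale, in the larger practice. So list size does not turn counts into shares.

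**2. Is one stratum redundant?** Matrix rank with 36 strata (18 five-year bands by sex; the number is assumed):

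| Columns with an intercept | Rank / columns | One stratum redundant? |
|---|---|---|
| 36 proportions | 36 / 37 | yes |
| 36 counts | 37 / 37 | no |
| 36 counts + linear list size | 37 / 38 | yes |
| 36 counts + list-size quintiles | 41 / 41 | no |

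The stated reason therefore holds for counts only in the third case, which the plan does not guarantee.

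**3. How much is lost?** This was simulated with 530 practices (Sample size section) allocated 1:1. The coefficient of variation (CV) of list size was 0.7, borrowed from the plan's CV for cancer cases per practice, with 0.4 as a variant. Assumed, because the document does not give them: mean list 9,000; SD of the share aged 65 and over about 6.5 points; between-practice SD 0.15–0.25 on the log scale; a contextual effect of 0–0.20 in log rate per SD of that share. The fit was a weighted practice-level log-rate regression, an approximation to the planned mixed Poisson model.

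*Information content.* For a single stratum, list size explains on average about 80% of the variance of the count, and the stratum's own proportion about 14%. Taken together, 35 counts explain 77% (adjusted 75%) of the variance in the share aged 65 and over; list size alone explains about 0%. A separate simulation (478 practices, 38 strata) gave adjusted R² for counts of 0.871, 0.817 and 0.713 at list-size CV 0.4, 0.5 and 0.7. Adding list size gave 0.872, 0.818 and 0.714.

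*Standard error (SE) of the arm effect*, both codings with list size included:

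| Contextual effect | Between-practice SD | List CV | Events per patient, 2 years | SE, counts | SE, proportions | Ratio |
|---|---|---|---|---|---|---|
| 0 | 0.25 | 0.7 | 0.07 | 0.0228 | 0.0228 | 1.000 |
| 0.05 | 0.25 | 0.7 | 0.07 | 0.0231 | 0.0229 | 1.006 |
| 0.10 | 0.25 | 0.7 | 0.07 | 0.0234 | 0.0229 | 1.022 |
| 0.20 | 0.25 | 0.7 | 0.07 | 0.0248 | 0.0229 | 1.086 |
| 0.20 | 0.25 | 0.4 | 0.07 | 0.0237 | 0.0229 | 1.039 |
| 0.10 | 0.15 | 0.7 | 0.0026 (23/9,000) | 0.0252 | 0.0244 | 1.033 |

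With a true arm effect of zero, the mean estimate lay between −0.0022 and 0.0005 across both codings. The simulation error of such a mean is about 0.023/√300 = 0.0013, so there is no sign of bias. Other assumed settings with Poisson noise gave a loss of about 0–3% for contextual effects up to 0.10, and 3–13% at 0.20.

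**The case against.** The strongest reply is that the plan already does the important adjustment. Rates are analysed by age-sex stratum, with the stratum's age and sex always in the model, so the direct effect of composition is handled. The practice-level terms can pick up only a residual contextual effect, and they enter only if associated with the outcome. This stands, and it is why the loss is nil when there is no such effect.

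A reader might infer that the counts measure list size instead of mix. That holds, broadly, for one count at a time but not for the set: jointly they recover roughly 70–87% of the mix variation in the simulations, while list size alone recovers about none. For the same reason, it misleads to point out that a young large practice and an old small one can have the same number of older patients. The other strata enter too and tell the two apart.

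A reader might also infer that the reason for omitting a stratum is simply wrong. It is not. List size is named in the preceding sentence, and if it enters linearly the omitted count equals list size minus the rest. The reason fails only if list size is not selected or is categorised, and even then just one of some 36 columns is lost.

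Finally, the size of the loss rests on assumptions. The CV of 0.7 describes staged cancer cases per practice and may overstate the variation in list size. The simulated effect is linear in a share, which favours proportions. Poisson error dilutes the loss. Take mix as explaining 30% of between-practice variance and counts as capturing 0.713 of that. With no Poisson error the SE ratio is √[(1 − 0.3×0.713)/(1 − 0.3)] = 1.060. With 23 cases per practice (variance 1/23 = 0.0435) and an assumed between-practice SD of 0.20 (variance 0.04), it is √[(0.0435 + 0.04×0.786)/(0.0435 + 0.04×0.70)] = 1.024. These points stand as limits on the magnitude. They do not make counts the better coding.

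**Conclusion.** The point holds as a minor improvement. The article itself fixes the coding as counts, so this is not a detail left to an analysis plan. That coding confounds size with mix in a model for rates, and the stated reason for omitting a stratum is secure only for proportions.

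The cost is precision alone: none without a contextual case-mix effect, typically 0–3% of the arm-effect standard error, and about 3–13% if that effect is as strong as 0.20 per SD. All of these figures rest on assumed inputs that the document cannot settle. The documents do not support any claim of bias, because allocation is randomised. The primary stage analysis is unaffected, since it has no case-mix term of this kind.

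**What to change.** In the rate-outcome paragraph of Data analysis, replace counts by proportions: the number of patients in each 5-year age-by-sex stratum divided by the practice list size, with one stratum left out. Keep list size as a separate term. The exclusion is then exact whether or not list size is selected, and the entry rule tests mix and size separately.

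If counts are kept, the minimum is to state that list size always accompanies them as a linear term. That secures the reason for the exclusion but leaves the scale problem.

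The cost is one word in the plan and one division in the derivation code. The stratum populations are already needed as denominators for the stratum rates, so no new data are required.
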